### Data analysis

Data will be blinded during the analysis, and the blinding will not be broken before two conclusions are drawn (i.e., the first assumes treatment A to be quetiapine and treatment B to be the aripiprazole; the second is based on the reverse assumption, i.e., that treatment A is aripiprazole and B is quetiapine) [82]. A detailed protocol for the statistical analysis plan will be presented in a separate paper. In short, the primary analysis will be according to the modified intention-to-treat principle [83] with adjustment for the protocol specified stratification variables [84]. Data missingness will be investigated and if deemed necessary, generally when missingness is not completely at random, a suitable multiple imputation method will be used [85-92]. The data will be analysed with a two-sided statistical testing and p-values will be assessed at a significance level of 5% with correction for multiple testing according to Holm [93]. Covariates considered relevant to adjust for in comparative analysis will be incorporated in the statistical model. We aim at analysing the data as trajectories including multiple assessments whenever possible.

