**Methods/Design:**

The TEA trial is a Danish investigator-initiated, independently funded, multi-centre, randomised, blinded clinical trial. Based on sample size estimation, 112 patients aged 12-17 years with psychosis, antipsychotic-naïve or treated for a limited period are, 1:1 randomised to a 12- week, double-blind intervention with quetiapine versus aripiprazole. Effects on psychopathology, cognition, health-related quality of life, and adverse events are assessed 2, 4, and 12 weeks after randomisation. The primary outcome is change in the positive symptom score of the Positive and Negative Syndrome Scale. The recruitment period is 2010-2014.

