### Randomisation and blinding

Randomisation of patients to treatment is carried out centrally by the Copenhagen Trial Unit at the Capital Region Pharmacy using a computer-generated allocation sequence with a block size unknown to the investigators. To optimise the comparability between treatment groups, randomisation is stratified by two factors: PANSS-P score (i.e., ≤20 points or >20 points), and age (i.e., 12-14 years or 15-17 years). Computer-generated and sealed allocation sequence lists are prepared according to the stratification variables and the trial medication packages are distributed accordingly. The interventions are blinded to participants, caregivers, outcome assessors, statisticians, conclusion drawers, as well as all investigators and staff involved in the trial, except for the pharmacy personnel who pack and distribute the two study drugs and the data managers at the Copenhagen Trial Unit.

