Based on results from a 24 weeks RCT comparing olanzapine with quetiapine that found a mean difference in PANNS-P scores of 4 points in favour of olanzapine (a difference that did not reach significance probably due to the small group size of 25 patients each) [20], we decided that a minimal clinically relevant difference between outcome responses of quetiapine vs aripiprazole after (the shorter period of) 12 weeks of treatment would be 3 points on the PANSS-P. Hence, using a power of 80% and a two-sided alpha of 5%, and expecting a SD of 5.7 on the PANSS-P, the required sample size necessary to detect or reject a difference of at least 3 points on PANSS-P was estimated as follows (N = total sample size, SD of the primary outcome measure = 5.7 (we assume SD_1_ = SD_2_), α = type 1 error = 0.05, β = type 2 error = 0.20, MIREDIF = minimal relevant difference of outcome measure = 3, z = fractiles in normal distribution): *N = 2 * (SD*_*1*_^*2*^ *+ SD*_*2*_^*2*^*) * (z*_α*/2*_ *+ z*_β_*)/MIREDIF*^*2*^ *= 112.* Accordingly, we should strive to include a total of 112 patients, equivalent to about 56 patients in each of the intervention groups.

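### The only baseline adjustment named for the primary analysis is the dichotomised PANSS-P stratum; the recorded score would give more precision at no cost

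*Protocol article*

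**What the plan says.** The Data analysis section describes a modified intention-to-treat primary analysis "with adjustment for the protocol specified stratification variables". The Randomisation and blinding section defines those variables as "PANSS-P score (i.e., ≤20 points or >20 points), and age (i.e., 12-14 years or 15-17 years". Table 1 schedules the PANSS at week 0 and at weeks 2, 4 and 12, so each patient's baseline score is available as a number.

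Three other statements bear on how baseline enters the model:
- The abstract defines the outcome as a difference from baseline: "The primary outcome is change in the positive symptom score of the Positive and Negative Syndrome Scale".
- The Data analysis section states a longitudinal aim: "We aim at analysing the data as trajectories including multiple assessments whenever possible".
- The same section leaves room for further covariates: "Covariates considered relevant to adjust for in comparative analysis will be incorporated in the statistical model".

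None of these names continuous baseline PANSS-P as a covariate. Details are deferred: "A detailed protocol for the statistical analysis plan will be presented in a separate paper".

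**The concern.** The baseline value of an outcome scale is usually among the best predictors of its later value. Reducing it to two groups treats a patient scoring 21 like one scoring 35, and separates patients scoring 20 and 21. Variation in baseline within each stratum then stays in the residual, as does any chance imbalance between arms within strata.

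At stake is precision in a trial that can no longer add patients cheaply. The discussion of sample size reports that all 112 patients have been included after slow recruitment, and the Strengths and limitations section accepts that higher variation than expected may limit power. A better use of data already collected is one of the few remaining ways to gain precision.

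**Working it through.** **1. The plan's own figure.** The Sample size estimation section sets out its inputs as "using a power of 80% and a two-sided alpha of 5%, and expecting a SD of 5.7 on the PANSS-P", with a minimal relevant difference of 3.
- With z values 1.960 and 0.842: N = 4 × (1.960 + 0.842)² × (5.7/3)² = 113.3, or 57 per arm (114) after rounding up.
- With Table 4's rounded multiplier: 31 × (5.7/3)² = 111.9, so the stated 112 reproduces.
- Power at 56 per arm, normal approximation: Φ(3 / (5.7 × √(2/56)) − 1.96) = 79.5%. No covariate gain is built in.

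**2. What the split keeps.** Assume a normal baseline with mean 22.5 (Table 3 means run from 21.4 to 23.8) and SD 5.1 (the Danish sample cited under Sample size estimation), cut at 20.5 because scores are whole numbers.
- Standardised cut c = (20.5 − 22.5)/5.1 = −0.392.
- Share at or below 20: p = 0.347. Normal density at c: 0.369.
- Share of the baseline-explained variance kept: k = 0.369² / (0.347 × 0.653) = 0.60.

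**3. A guide to the correlation.** The article reports no correlation r between baseline and week 12. In Table 3, the aripiprazole 10 mg arm has baseline SD 5.0, follow-up SD 6.0 and change SD 6.0, so r = (25 + 36 − 36)/(2 × 5 × 6) = 0.42. This is weak evidence: both later SDs are back-calculated from an SE printed as 0.6. If each SE may lie anywhere from 0.55 to 0.65, r can lie between about 0.24 and 0.57. A range is therefore needed.

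**4. Gain from the continuous score, 56 per arm, difference 3.**

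*Reading (a): 5.7 is the SD of the week-12 score.* Residual SD is 5.7√(1 − kr²) with the stratum and 5.7√(1 − r²) with the score.

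| r | SD, stratum | SD, continuous | Variance cut | Power |
|---|---|---|---|---|
| 0.3 | 5.54 | 5.44 | 3.8% | 81.7% → 83.1% |
| 0.4 | 5.42 | 5.22 | 7.0% | 83.4% → 86.0% |
| 0.5 | 5.25 | 4.94 | 11.7% | 85.6% → 89.5% |
| 0.6 | 5.04 | 4.56 | 18.3% | 88.2% → 93.6% |

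*Reading (b): 5.7 is the SD of change, as the discussion of sample size says, and change is analysed.* The follow-up SD s solves s² − 2r(5.1)s + 5.1² − 5.7² = 0. The correlation of baseline with change is q = (rs − 5.1)/5.7. Residual SD is 5.7√(1 − kq²) with the stratum and s√(1 − r²) with the score.

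| r | SD, stratum | SD, continuous | Variance cut | Power |
|---|---|---|---|---|
| 0.3 | 4.90 | 4.29 | 23.3% | 89.9% → 95.9% |
| 0.4 | 5.21 | 4.86 | 13.0% | 86.1% → 90.4% |
| 0.5 | 5.48 | 5.33 | 5.4% | 82.6% → 84.6% |
| 0.6 | 5.66 | 5.63 | 1.0% | 80.1% → 80.5% |

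The two readings trend in opposite directions. Near r = 0.4 they give 7-13% of variance and roughly 3-4 points of power.

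**5. Does analysing change already recover this?** Not in general. With the SDs in step 3, change has the same SD as follow-up (6.0), and its correlation with baseline is (0.417 × 6 − 5)/6 = −0.42. Subtracting baseline gains nothing there. For either outcome the residual SD is 5.68 with the stratum and 5.45 with the score, a variance cut of about 8%.

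**The case against.** The strongest reply is that nothing stated is wrong. Adjusting for the factors used in stratified randomisation is valid and standard, and chance imbalance within strata is not bias. The Data analysis section is a summary that defers to a separate paper, and the functional form of baseline could be settled there. The outcome is a change score, trajectories are intended, and the clause on relevant covariates could admit the continuous score. The correlation is poorly supported.

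Much of this stands, and it limits the point to efficiency. It does not remove it. The article does make a choice of adjustment, and the choice it names uses the cruder form of a variable it measures exactly. Neither the change score, nor the trajectory aim, nor the deferral supplies adjustment for the continuous baseline.

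Two stronger readings should be resisted:
- A reader might infer that baseline PANSS-P enters *only* as the stratum. The text does not say so, and it does not exclude the continuous score.
- A reader might infer from the open covariate clause that the primary model will be chosen after the data are seen. The article gives no timing for that choice. It leaves the detail to the separate analysis plan, and it states: "Data will be blinded during the analysis, and the blinding will not be broken before two conclusions are drawn". Blinding does not replace prespecification, but the closed covariate list belongs to that plan and is no part of this point.

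**Conclusion.** The point holds as a modest, cost-free improvement in precision. It rests on a roughly normal baseline near the Table 3 values and on an assumed correlation; across r = 0.3-0.6 the saving runs from about 1% to 23% of residual variance, depending on r and on what the 5.7 describes.

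It should not be read as a power shortfall. The 79.5% at 56 per arm is an unadjusted figure, and adjustment by stratum already improves on it under these assumptions. At the planning SD of 5.7 read as the week-12 SD and r = 0.42, the comparison is about 84% with the stratum against 86-87% with the continuous score. N = 112 does not change, and the treatment estimate is not biased by using the stratum.

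**What to change.** State that the primary model, whether for week-12 PANSS-P, for change, or as a trajectory model, adjusts for continuous baseline PANSS-P in place of or in addition to the PANSS-P stratum, together with the age stratum. Keeping the stratum alongside the score respects the randomisation scheme and costs one degree of freedom.

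This is one sentence in the analysis plan, to be fixed before outcome data are analysed. It needs no new data, no extra visits and no change to the sample size.

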### Ethical considerations

As the trial is investigating medicinal products and the participants are under 18 years of age, a surrogate written informed consent is required from the holders of custody. The trial is registered at ClinicalTrials.gov: NCT01119014, EudraCT: 2009-016715-38, and approved by Danish Medicines Agency: 2612-4168, The Ethics Committee of Capital Region: H-3-2009-123 and Danish Data Protection Agency: 2009-41-3991. All procedures for registering and reporting adverse reactions and adverse events will follow the regulations and guidelines from the Danish Health and Medicines Authority and the Ethics Committee.

## Discussion

### Legitimacy of the trial

The use of antipsychotics in children and adolescents is rising in many countries [94-97]. In Denmark, the number of persons aged 0-18 years treated with antipsychotics (all indications) increased by a factor four from 1999 to 2012 [98]. Secondly, off-label use is prevalent. In the United States, five newer antipsychotics (aripiprazole, olanzapine, paliperidone, quetiapine, and risperidone) are currently approved for schizophrenia in children aged 13 to 17, but in the EU until recently only one compound (aripiprazole) has been approved for the use in schizophrenia from age 15 (in June 2014 paliperidone was approved for the same indication [99]). The off-label use in paediatric populations is of major concern to the EMA which calls for randomised trials [100]. Thirdly, in child- and adolescent psychiatry only seven double-blinded RCTs comparing antipsychotics for the treatment of child- and adolescent psychosis have been carried out, and since the clinical effects vary between compounds and among patients, there is no doubt that RCTs including large samples are lacking in this field. Specifically, to date no RCTs investigated quetiapine vs aripiprazole in EOP. Notably, even in adults, no RCT outside of China has compared quetiapine vs aripiprazole for the treatment of psychosis either [51]. Moreover, more frequent and severe adverse effects that can have potential long-term consequences, i.e., metabolic syndrome, may be expected in young patients [8,101].

### Time frame

A challenge in clinical practice and in trials is to identify the relevant time frame for assessing the effectiveness of antipsychotic treatment. We decided to investigate as our primary outcome the antipsychotic response after 12 weeks of treatment. In clinical practice, the usual routine is to continue treatment with an antipsychotic drug for a period of at least 4 - 6 weeks to evaluate the antipsychotic response. This individual drug trial period is partly arbitrarily defined [102-105] based on older preclinical studies [106]. However, brain imaging studies of both FGAs and SGAs have shown that dopamine D2 receptor occupancy occurs within hours after administration [107,108], and clinical antipsychotic effects can be distinguished from non-specific sedative effects within the first 24 hours of treatment [104]. Studies in adults have demonstrated that the largest effect of antipsychotics occur during the first four weeks of treatment [103,109], and that the early response after 4 weeks can predict long-term effects [105]. The only two studies on this issue in EOP found that early response to aripiprazole after 3 weeks predicted well ultimate response at 6 weeks in an RCT including youth with schizophrenia [51,110,111] and that early response to mixed SGAs after 4 weeks predicted response at week 12 in naturalistically treated youth with schizophrenia spectrum disorders [112]. In order to further investigate the early clinical response as a predictor of later clinically significant effects on psychopathology, we decided to measure treatment responses after 2, 4 and 12 weeks of treatment in the randomised, blinded design, and to measure the long-term effects in a naturalistic design with follow-up at 1 year after randomisation.

### Sample size estimation

The key consideration in designing a RCT is to know the size of a sample needed to obtain limited probability of type 1 (false positive) and type 2 (false negative) errors. The sample size estimation is based on choices regarding an acceptable risk of type 1 and 2 errors, on assumptions regarding the variation in outcome measures, and finally on the estimation of the minimal relevant difference in clinical effect between the interventions under the trial. Thus, the following four variables were considered:

1) α or type 1 error (the probability of rejecting the null hypothesis when it is actually true) is usually set at 0.05 two-sided. If we find a difference below this level we may declare a significant difference, knowing that there will still be a 5% risk that the null hypothesis of no difference is correct.

2) We decided in our updated sample size estimation to use a value of 80% for power, which is standard and translates into accepting a 20% risk that we will miss a true difference of the anticipated magnitude between the two compounds of (in this case) 3 points on the PANSS-P scale.

3) The expected variation in the primary outcome measure PANSS-P was initially driven by the only three relevant RCTs (upper three studies in Table 3) that were available in 2009 [11,20,71]. During our recruitment in the TEA trial, more informative studies have appeared (lower three studies in Table 3), i.e., two published RCTs [15,21] and one RCT reported to clinicaltrials.gov [28]. Based on a weighted mean SD of change in PANSS-P scores from all six trials, we used in our updated sample size calculation a SD of 5.7 on the PANSS-P scale.

4) MIREDIF should represent a meaningful minimal difference in response in the sense that it would justify a choice between two interventions in a clinical setting. The PANSS-P scale scores range from 7 to 49, and the few relevant RCTs already conducted found that the mean PANSS-P score after 6 weeks to 6 months of treatment is around 15 in the aripiprazole or quetiapine groups with a mean PANSS-P score change in the range 6.2–9.6. For the TEA trial, we decided in our updated sample size estimation, based on data from a head-to-head trial comparing olanzapine vs quetiapine in EOS [20], that it would be clinically relevant to be able to detect a difference of 3 points in outcome score on the PANSS-P scale between the two drugs.

Underpowered trials bear the risk of both type 1 and type 2 errors. On the other hand, an unnecessarily large sample size wastes resources, from participants and researchers and may increase risk of type 1 error, by rejecting the null hypothesis in favor of small significant effects that are clinically meaningless [113]. Challenges regarding sample size calculations often, as in this trial, stem from uncertainty concerning parameter estimates due to limited information prior to the launch of the trial. Deciding on the values of the parameters included in the sample size estimation are crucial, since relatively small changes in best estimates of variance of the outcomes, and in choice of size of clinical relevant differences in outcomes, power or α demands can alter the sample size needed. Table 4 gives some examples, including both our original and our updated sample size estimation, and shows the effects of variation in variables on the sample size.

**Table 4 T4:** Sample size estimation

	**β**	**SD**	**MIREDIF**	**Effect size**	**Calculations:**** N = 4 * (z**_**α/2**_ **+ z**_**β**_**)**^**2**^** * (SD**_**1**_**/MIREDIF)**^**2 #**^	**N**
*TEA original*	*0.10*	*7.4*	*3.5*	*0.47*	*N = 42 * (7.4 / 3.5)*^ *2* ^	*188*
TEA smaller MIREDIF	0.10	7.4	2.0	0.27	N = 42 * (7.4 / 2.0)^2^	575
TEA larger MIREDIF	0.10	7.4	5.0	0.67	N = 42 * (7.4 / 5.0)^2^	92
TEA larger SD	0.10	10.0	3.5	0.35	N = 42 * (10.0 / 3.5)^2^	343
TEA smaller SD	0.10	5.7	3.5	0.61	N = 42 * (5.7 / 3.5)^2^	111
TEA larger β	0.20	7.4	3.5	0.47	N = 31 * (7.4 / 3.5)^2^	139
*TEA updated larger* β*, smaller SD, smaller MIREDIF*	*0.20*	*5.7*	*3.0*	*0.53*	*N = 31 * (5.7 / 3.0)*^ *2* ^	*112*

The original and the updated TEA calculations and examples of different values of MERIDIF (minimally relevant difference), SD (standard deviation) and β (risk of type II error) are shown. As can be seen, the larger the MIREDIF you wish/expect to be able to detect or the smaller the estimated SD of the outcome measures or the larger the β, the smaller the sample size needed. In these calculations we used a two-sided α (risk of type I error) = 0.05 and we assumed SD_1_ = SD_2_. Effects sizes depend on MIREDIF and SD. Compared to the original calculation, the updated sample size calculation is balanced by allowing for a larger β, expecting a zsmaller SD and lowering the detectable MIREDIF. z = fractiles in normal distribution. ^#^N = 2 * (SD_1_ ^2^ + SD_2_ ^2^) * (z_α/2_ + z_β_)/MIREDIF^2^ ⇒ N = 4 * (z_α/2_ + z_β_)^2^ * (SD_1_/MIREDIF)^2^. The product 4 * (z_α/2_ + z_β_)^2^ is rounded up to whole figures in the equations.

Another challenge encouraging us to update our sample size estimation was the slow participant recruitment, as also demonstrated in other RCTs in child- and adolescent psychiatry [27]. Our original sample size (based on an estimated PANSS-P SD of 7.4, a MIREDIF of 3.5 and power of 90%) of n = 188 was expected to be recruited during a 2 year period from mid-2010. This expectation was based on available statistical data from the Danish Psychiatric Central Register concerning the incidence of first-episode psychosis in the involved geographical areas, whereof we expected to be able to randomise 50%. However, the recruitment turned out to be slower, primarily due to administrative difficulties in implementing the trial protocol in all centres. Adjustment of the sample size during the course of a clinical trial is a potential strategy to meet such challenges. We chose to update our sample size estimation by 1) adjusting the estimated SD of our primary outcome measure, change in PANSS-P, to a score of 5.7, based empirically on new relevant data from additional studies in the field that were relatively large and happened to report lower SDs, 2) changing the power from 90% to the more conventionally used 80%, and 3) lowering the MIREDIF from 3.5 to 3.0. As a result of these adjustments our updated sample size estimation still aims at detecting a difference between the two interventions on the primary outcome measure of a medium effect size of around 0.5, which is considered clinically relevant. At present, we have included all n = 112 patients during a recruitment period of 3½ years, and the last randomised patients are terminating the blinded treatment.

We believe that the updated sample size estimation is based on as accurate variables as possible, with the same conservative value for α, a value of SD, which is based on the most updated empirical body of evidence, and relevant estimates for the expected MIREDIF and effect size. We expect one agent being superior to the other by a score of 3 on the change in PANSS-P, which is in line with Arango et al. [20]. If the mean SD turns out to be higher than 5.7, we will use the statistical principles of interim analysis [114] to control for random errors. We will analyse the data by using the intention-to-treat principles and application of multiple imputations for missing data as outlined above.

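### Switching to interim-analysis principles if the SD exceeds 5.7 corrects no type I error, conflicts with the stated 5% level and can only cost power

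*Protocol article*

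**What the plan says.** The updated sample size calculation (Methods, Sample size estimation) is set out as "using a power of 80% and a two-sided alpha of 5" per cent, a minimal relevant difference after "12 weeks of treatment would be 3 points on the PANSS-P", and "expecting a SD of 5.7 on the PANSS-P". The resulting total is 112, about 56 per arm.

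The Discussion section of the same name then adds a condition: "If the mean SD turns out to be higher than 5.7, we will use the statistical principles of interim analysis". The stated purpose is control of random errors. The paragraph before it reports that accrual is finished: "At present, we have included all n = 112 patients during a recruitment period of 3½ years".

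Three other places bear on the rule:

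- Methods, Data analysis: two-sided tests at the 5% level with Holm correction. Nothing there depends on the observed SD.
- Discussion, Sample size estimation: low power is said to carry a risk of type 1 as well as type 2 error. The same section says the alpha value was left unchanged when the sample size was updated.
- Discussion, Strengths and limitations: a higher variation than expected is said to limit power. Type I error is not mentioned.

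**The concern.** Sequential boundaries exist because testing accumulating data repeatedly at 5% raises the overall false-positive rate. The article describes a single test on a complete sample, so there is no repetition to pay for. An SD above the planning value is a shortfall of information. It widens the standard error and costs power, and the test already allows for it.

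Under the rule, the level of the primary test would be known only once the SD has been estimated, and it would be strictest when power is already short. The trigger is also loose. The article does not say whether the mean SD is that of baseline, week-12 or change scores, or whether it is pooled or per arm. Its Table 3 gives weighted means of 5.48 for all SDs and 5.68 for change scores, so the choice matters around 5.7.

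**Working it through.** **Inputs.** Difference 3, SD 5.7, two-sided alpha 0.05, power 80%, total 112 (Methods, Sample size estimation); 1:1 allocation (Abstract), hence 56 per arm. Larger SDs to try: 6.3, the top of the range that the article gives for the newer studies; 7.4, its original planning value; and 7.0 in between.

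**The plan's own figure.** Table 4 uses N = 4(z_α/2 + z_β)²(SD/MIREDIF)². With its rounded constant, 31 × (5.7/3)² = 111.9, i.e. 112. With the unrounded constant, 4 × (1.960 + 0.842)² = 31.40 and N = 113.3. The figure reproduces. (The formula printed in Methods lacks the square on the z term; the squared form of Table 4 is used here.)

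**Is there any type I error to correct?** Two-sample t-test, 56 per arm, no true difference, 2 million replicates per scenario. Rejection rate at 5%:

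- true SD 5.7, 6.3, 7.0, 7.4: 5.0% in each case;
- true SD 5.7, only the trials with observed SD above 5.7: 3.7%.

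There is no excess. Where the rule would be triggered at a true SD of 5.7, the plain test is already below 5%.

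**What would the rule cost?** The article names no boundary, so two standard spending functions are assumed. The information fraction is t = 112/N(SD), with N(SD) = 31.40 × (SD/3)².

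- O'Brien-Fleming-type: α(t) = 2[1 − Φ(1.960/√t)]
- Pocock-type: α(t) = 0.05 × ln[1 + (e − 1)t]

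Example at SD 6.3: N = 31.40 × 4.41 = 138.5; t = 112/138.5 = 0.809. The O'Brien-Fleming-type level is 2[1 − Φ(2.179)] = 0.029. The Pocock-type level is 0.05 × ln(2.390) = 0.044.

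Power is from the noncentral t distribution with 110 degrees of freedom and noncentrality 3/(SD × √(2/56)), with the level fixed at the SD shown:

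| SD | N needed | t | α, OBF-type | α, Pocock-type | Power at 5% | Power, OBF-type | Power, Pocock-type |
|---|---|---|---|---|---|---|---|
| 6.3 | 138.5 | 0.81 | 0.029 | 0.044 | 70.5% | 62.3% | 68.4% |
| 7.0 | 170.9 | 0.66 | 0.016 | 0.038 | 61.3% | 42.7% | 56.7% |
| 7.4 | 191.0 | 0.59 | 0.011 | 0.035 | 56.6% | 32.8% | 50.5% |

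Simulating the whole rule, with the level recomputed from each trial's observed SD, gives nearly the same power: 61.7% and 68.3% at true SD 6.3, 42.8% and 56.6% at 7.0, 33.3% and 50.5% at 7.4. Type I error under the rule is 3.3% and 4.5% at 6.3, and 1.4% and 3.6% at 7.4 (O'Brien-Fleming-type and Pocock-type respectively).

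**How often would it be triggered?** For a pooled SD on 110 degrees of freedom, P(observed SD > 5.7) is 48% if the true SD is 5.7, 26% if it is 5.48 and 92% if it is 6.3.

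**The case against.** The strongest reply is that the sentence does little harm. An adjustment of this kind can only tighten the threshold. The SD is a nuisance parameter that can be estimated on blinded data, so the treatment difference does not steer the level. The Data analysis section carries no such condition and leaves detail to a separate plan, where a boundary would belong. The cited source for the interim-analysis principles is not available here. All of this stands, and it lowers the severity.

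The figures also need care. Under Pocock-type spending the loss is only about 2 points at SD 6.3 and 6 at 7.4, against 8 or 9 and 23 or 24 under O'Brien-Fleming-type. SDs of 7.0 and 7.4 lie above the 4.3 to 6.3 that the article gives for the newer studies. The calculation uses an unadjusted t-test, whereas the plan adjusts for the stratification variables; a residual SD could be lower, with fewer triggers.

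A reader might infer four stronger things that the documents do not support:

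- *That the rule inflates false positives.* It does the reverse.
- *That the 5% in the sample size sections is the analysis commitment.* There it is a planning input. The commitment that the rule conflicts with is in Data analysis.
- *That an adjustment is owed because the trial was resized from 188 to 112.* The article attributes that change to external studies and slow recruitment, not to unblinded trial data.
- *That the remark about an unnecessarily large trial, which "may increase risk of type 1 error, by rejecting the null hypothesis in favor of small significant effects", explains the rule.* It concerns too much information, while the rule responds to too little. The nearer rationale is the sentence that underpowered trials risk type 1 error, and that does not justify the rule either.

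None of this rescues the rule. It is a stated rule that conflicts with another section, not a missing detail, and the loss runs in the same direction under either boundary. If the 112 patients were treated as a first look at a larger trial, the withheld alpha would never be spent, because no later look is described.

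**Conclusion.** The point holds. With one analysis of a complete sample, an SD above 5.7 reduces power and leaves type I error at 5%. The rule therefore corrects nothing, conflicts with the unconditional level in Data analysis, and makes the primary threshold depend on an SD whose definition is left open.

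The direction of the cost does not depend on the boundary; its size does. For a 3-point difference the loss is roughly 2 to 9 percentage points at SD 6.3, 5 to 19 at SD 7.0 and 6 to 24 at SD 7.4. These figures assume 56 analysed patients per arm, an unadjusted comparison, and an information fraction of 112 over the sample size needed at the observed SD. Missing data would lower every power figure.

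The conclusion that no adjustment is needed rests on there having been no interim look, further accrual or unblinded resizing; the article describes none. As the rule is conservative, this should be fixed before unblinding, but it does not threaten the validity of a positive result.

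**What to change.** Delete the sentence and state instead that there is one final analysis, at the two-sided 5% level and under the multiplicity procedure of the Data analysis section, whatever SD is observed. Add that the observed SD and the 95% confidence interval for the treatment difference will be reported, so that lost precision shows in the width of the interval. Keep the Holm correction in the wording; a bare statement of a 5% test would leave its relation to the primary outcome unclear.

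The cost is one sentence, carried into the separate analysis plan. By the article's account the last randomised patients are only now finishing blinded treatment, so the change can be made and dated before the code is broken. If any interim look or unblinded resizing did take place, it should be disclosed and the adjustment based on that, not on the SD.
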